### Co-enrollment

Possible simultaneous co-enrollment to any other RCT will be discussed by the Management Committee.

### Timeline

Trial sites determined – September 2015

Governance approval applications submitted – October 2015

First participant enrolled – April 2016

Last participant enrolled – November 2017

Follow-up completed – December 2017

Data analysis and submission for the main publication – March 2018

Laboratory analyses completed – June 2018

Publications of clinical sub-studies and laboratory analyses completed – December 2018

### Laboratory measurements

Ethylenediaminetetraacetic acid (EDTA) plasma samples and whole blood will be drawn as soon as possible after ICU admission, and at 72 h from ICU admission for later analysis of patient-related changes in biomarkers indicating endothelial/myocardial damage, such as CD73 and vascular adhesion protein-1 (VAP-1), heparin-binding protein (HBP), chromogranin A (CgA), metabolomics, and mitochondrial function tests.

### Publication plan

All trial results whether positive, negative, or neutral will end up in the public domain, preferably in a peer-reviewed publication. All trial sites with at least 25 randomized patients will be granted one authorship for the site PI, and each additional 25 patients will guarantee one additional authorship for the site AIs. A trial statistician (TL) will also be granted an authorship. The order of authorships for the study main publication will be as follows: VP, SJ, and AP will be the first, second, and third, and JT the last author. Other authors will be in the order of included number of patients with high-quality data: site PIs first, and AIs thereafter. The authorships for the publications of the main and sub-studies will follow the International Committee of Medical Journals Editors’ (ICMJE) principles. The full protocol and the participant-level anonymized dataset will be submitted as appendices with the main paper to be publicly available after the study publication. The SPIRIT checklist for clinical trial protocol is provided as Additional file 1.

### Perspectives

Septic shock affects millions of patients worldwide annually. The results of study will – in any case – have a major influence on the clinical management/international guidelines regarding treatment of septic shock. If supporting our hypothesis of the beneficial effects of TTP, the current recommendations will have to be changed leading to major scientific and societal impacts on heath and health care costs. In case MCG proves to be better, the study results will for the first time confirm the widely recommended minimum MAP level. Given that several different pathophysiological pathways are probably in interaction and may only partly explain the clinical course of the disease, the potential strength of measuring several biomarkers/mitochondrial function/gene expression and protein synthesis in the sub-studies of this phase II study, will give us the opportunity to compare their relative importance and predictive power with regard to organ dysfunction.

## Discussion

Conduct of the TARTARE-2S trial is in broad agreement with the international guidelines [7] regarding the control group. The targeted patient population fulfills the recent Sepsis-3 septic shock definition [27], representing the most severely ill septic shock patients with plausibly the highest possible chance to show a difference between the intervention arms [28], if such a difference exists. The experimental approach is supported by a recent review [9] highlighting the paucity of evidence to support the guidelines and additional evidence suggesting the relevance of more detailed monitoring of peripheral perfusion [13, 14] to guide the treatment in septic shock. The TARTARE-2S trial may be one of the first trials to bridge the gap between evidence and clinical practice and to provide detailed data on efficacy and safety of TTP to guide treatment in patients with septic shock.

## Trial status

Patient recruitment has started in May 2016. Ethics and hospital approvals have been granted in Finland, and in Switzerland, and have been applied in Denmark (as of July 28, 2016).

## Appendix 1 The trial criteria for septic shock

*Septic shock* is defined as:

1. Infection (suspected or documented) *and*
2. Systemic mean blood pressure above 65 mmHg requiring any dose of vasopressors (norepinephrine, vasopressin) despite adequate fluid resuscitation (minimum of 20 ml/kg (actual body weight) crystalloids) *and*
3. Elevated lactate ≥3.0 mmol/L with suspected hypoperfusion

## Appendix 2

**Table 2 Tab2:** The trial targets for the treatment arms. (Register hourly up to 24 h (every 2 h thereafter until study endpoint using tick boxes for targets)

I. Intervention group – targeted tissue perfusion (TTP) care:	
Primary targets	
Capillary refill time (CRT)/every hour	<3 s
Skin mottling [17]/every hour	Absent
Peripheral temperature/every hour	Warm
Urine output/every hour	≥0.5 mL/kg/h
Arterial lactate [7]/per 2 h	<2.0 mmol/L
Mean arterial pressure (MAP)	50–65 mmHg (minimum as a safety limit)
^a^If previous hypertension [7]	^a^65–70 mmHg
^b^If oliguria <0.3 ml/kg [7]	^b^2-h trial 75–80 mmHg,
	If diuresis improves, continue for 2 h and re-evaluate
Secondary target	
Continuous SvO_2_ [7], if available	>65 %^c^
II. Control group – macrocirculatory targets-guided (MCG) standard care	
Primary targets	
Mean arterial pressure (MAP) [7]	65–75 mmHg
^a^If previous hypertension [7]	^a^75–80 mmHg
^b^If oliguria <0.3 ml/kg	^b^2-h trial 85–90 mmHg
	If diuresis better, continue for 2 h and re-evaluate
Central venous pressure (CVP) [7]	8–12 mmHg
	Adequate fluid therapy is indicated to restore clinical hypovolemia up to the recommended CVP level of 8–12 mmHg, if needed
Urine output [7]	≥0.5 mL/kg/h
Secondary target	
Continuous SvO_2_ [7], if available	>65 %^c^

Dellinger et al. [7] according to the SSCG – Surviving Sepsis Campaign Guidelines: MAP, CVP, diuresis, SvO_2_ – 1C, lactate – 2C (1 – a recommendation, 2 – a suggestion, C – low level of evidence)

^a^Higher MAP targets may be required for septic shock patients with previous hypertension; ^b^and a test of providing higher MAP target for 2 h is recommended for those with oliguria

^b^The treating physicians should target to the lowest possible vasopressor use to maintain the highlighted lowest possible MAP level in each treatment arm; however, allowing individual higher MAP targets with specific reasons

^c^Measuring of ScVO_2_ is not recommended [1, 4, 5]. If monitoring is clinically required, use of a pulmonary artery catheter (PAC) is recommended. Pulse continuous cardiac output (PICCO) may be used for thermodilution cardiac output measurements

## Appendix 3

**Table 3 Tab3:** Data to be gathered regarding each hemodynamic target and treatment decision/change. Indicate when treatment start or change (at the same time)

(a). Hemodynamic problem(s)	
Hemodynamic problem(s)	Tick
Hypovolemia	
Hypervolemia	
Inadequate flow/cardiac index (CI)	
Tachycardia	
Inadequate contractility	
Inadequate afterload/hypotension	
Excessive afterload/hypertension	
Excessive vasopressor dose	
(b). Given treatment(s)	
Treatment(s) given	Tick
Volume	
Diuretics	
Inotrope	
Inotrope decrease	
Inotrope increase	
Vasopressor increase	
Vasopressor decrease	
Beta-blocking agent	
Vasodilating agent	

## Appendix 4 Data to be registered

Data will be obtained in eCRFs from a combination of national registers and medical records. Bedside target list for treatment reasons and decisions will be implemented in the PDMS (*) at each site, if possible.

Baseline variables

- National identification number (if available)
- Sex
- Age at randomization
- Estimated height
- Measured (if not possible estimated) weight
- Comorbidities? Y/N (hypertension*, chronic heart failure*, previous myocardial infarction, previous stroke, chronic obstructive pulmonary disease*, diabetes*, hematological malignancy*, metastatic cancer*, AIDS*)
- Elective or emergency admission*
- Operative or non-operative admission*
- Site of infection (pulmonary/abdominal/urinary tract/soft tissue/other)
- Previous plasma/serum creatinine (7–365 days before hospital admission), if available

24-h from ICU admission:

- Values for Simplified Acute Physiology Score (SAPS II)*

Twenty-four hours before randomization

- Volume of resuscitation fluids (crystalloids, colloids and blood products specified in milliliters)
- Hemoglobin (lowest)*
- SOFA score *variables**

At randomization

- Norepinephrine dose and mean arterial pressure (MAP) at the same time
- Total fluids given in last 2 h
- Lactate (last value from the previous 2 h)

Continuously as 10-min medians in the first 72 h after randomization:

- Systolic arterial pressure*
- Mean arterial pressure*
- Central venous pressure*
- Heart rate*
- Peripheral oxygen saturation (SpO_2_)*
- Continuous central venous oxygen saturation, if available
- Continuous mixed venous saturation, if available
- Dose of norepinephrine*
- Dose of dobutamine*

One-hour intervals (for 72 h)

- Urinary output*
- Volume of given fluids
- CRT – only in the TTP group
- Assessment of upper arm temperature – only in the TTP group
- Assessment of skin mottling score – only in the TTP group

Two-hour intervals (for 72 h unless study endpoint reached)

- Arterial lactate measured in both groups

Four-hour intervals during the first 72 h after randomization (if not discharged from the ICU)

- Arterial blood gas tensions (PaO_2_, PaCO_2_), pH and base excess (BE)
- Calculated Mixed v-aCO_2_/Da-vO_2_-ratio (if pulmonary artery catheter, PAC)
- Cardiac index (if PAC)
- Stroke index (if PAC)

Daily in the first 7 days after randomization (if not discharged from the hospital):

- SOFA score variables*
- Total volume of fluids
- Estimated fluid balance
- Dose of glucocorticoids (not recommended)

Daily up to 30 days:

- On mechanical invasive- or non-invasive ventilation? Y/N
- Ventilator settings at 8 a.m. (PEEP, Pplat, Vt)
- Use of muscle relaxants during the last 24 h? Y/N
- Presence of acute kidney injury (AKI) according to KDIGO classification? Y/N/and stage (I–III)
- Use of renal replacement therapy? Y/N
- Use of vasopressors? Y/N
- Use of inotropic agents? Y/N
- Ischemic events
- SARs and SUSARs

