### Hypothesis

We hypothesize that targeting clinical tissue perfusion (the TTP arm) will decrease the use and untoward effects of vasopressors, and result in more days alive in 30 days with normal arterial blood lactate (first value of <2 mmol/L) *and* without any inotropic or vasopressor agent – compared to standard clinical care with preference of macrocirculatory targets (the MCG arm).

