### Intervention accountability

Every patient will be allocated a registration sheet to be kept in the site master file. The initials, birth date, screening number, time for randomization, and study arm will be included. The compliance of trial arm targets for each study patient will be checked hourly for the first 72 h, and clinical problems and given hemodynamic treatments will be registered until the study combined endpoint has been fulfilled, up to day 30. The originals for these documents will be kept as the study source data at each site.

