### Data to be registered

The continuous data on hemodynamic parameters will be registered as 10-min medians using electronic PMDS, when possible and otherwise registered each hour to 72 h. For other data please see “Appendix 4.” The Standard Protocol Items: Recommendations for Interventional Trials (SPIRIT) figure regarding study interventions and timing is provided as Fig. 2.

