## Appendix 5 A detailed study statistical analysis plan

The primary analysis of the primary outcome (as well as secondary outcomes b, c, d, e, f, h, i, and j) will be an unadjusted Mann-Whitney test. As a sensitivity analysis the *p* values will be recalculated using permutations within groups defined by site and the presence/absence of hypertension. This test is a non-parametric version of an ANOVA adjusted for site and presence/absence of hypertension. A total of 100,000 permutations will be conducted for each test. The effect sizes will be quantified by direct comparisons of the raw means between groups. Confidence intervals will determined by non-parametric bootstrapping to accommodate the highly non-normal distribution of the outcomes.

The secondary endpoint “a” will be assessed by a Cox model treating death before normalization of lactate as a competing event. The Cox model will be adjusted for site and presence/absence of hypertension. The effect size will be quantified using the adjusted hazard ratio.

The secondary outcome “g” will be assessed using Fisher’s exact test. Effect sizes will be analyzed using crude proportions along with standard normality approximation-based confidence intervals.

The exploratory endpoint (90-day survival) will be assessed using Fisher’s exact test. Effect sizes will be quantified using odds ratios from a logistic regression adjusted for site and the presence of hypertension. As a sensitivity analysis a Cox model of time to death will also be employed. The Cox model will be adjusted for site and the presence/absence of hypertension. Here, the effect size will be quantified using the adjusted hazard ratio. The assumption of proportional hazards will be assessed using Schoenfeld residuals. Finally, Kaplan-Meier plots will be produced.

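### Cumulative norepinephrine to day 5 is a secondary outcome, but the listed data collection records the dose only for the first 72 h

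*Protocol article*

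**What the plan says.** The article's Secondary outcome measures section lists, as its ninth item, the cumulative norepinephrine dose up to day 5. Appendix 5 letters the outcomes, so this is outcome i, and fixes its test: "secondary outcomes b, c, d, e, f, h, i, and j) will be an unadjusted Mann-Whitney test". Appendix 5 also says that effect sizes will be raw mean differences with bootstrap intervals.

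Appendix 4 sets out the data to be registered, with a time window for each block. "Dose of norepinephrine" stands in the block headed "Continuously as 10-min medians in the first 72 h after randomization"; a single dose reading is also taken at randomization. The main-text section Data to be registered gives the same limit for continuous hemodynamic data, which are "otherwise registered each hour to 72 h" where the electronic system cannot supply 10-min medians.

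Three listed items bear on vasopressors after 72 h:

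- The block headed "Daily in the first 7 days after randomization (if not discharged from the hospital)" holds SOFA variables, fluids, fluid balance and glucocorticoid dose.
- The daily block to day 30 has "Use of vasopressors? Y/N".
- Intervention accountability says that "given hemodynamic treatments will be registered until the study combined endpoint has been fulfilled, up to day 30". The form for this, in Appendix 3, is a set of tick boxes that includes vasopressor increase and decrease.

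**The concern.** The outcome needs a dose history to day 5, and the listed dose history stops at 72 h. A site that follows Appendix 4 exactly would hand the statistician no dose for the last part of the window. The analysis would then use totals silently cut at 72 h, treat the totals of patients still on the drug as missing, or go back to the charts late.

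This matters because the hypothesis opens with the claim that the tissue-perfusion strategy "will decrease the use and untoward effects of vasopressors", and outcome i is the only listed outcome that measures that use as a dose. The Ethical considerations section also makes separation between the two interventions a condition for a later phase III trial. If the control arm does stay on vasopressors longer, a cut at 72 h removes more drug from that arm and makes the measured separation too small.

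**Working it through.** **Windows side by side.** If day 5 means five 24-h periods from randomization, the outcome window is 120 h and 120 − 72 = 48 h is uncovered. If day 1 is the calendar day of randomization, the window ends between 96 and 120 h, and at least 96 − 72 = 24 h is uncovered. Neither reading closes the gap.

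**Can the later items fill it?** The daily yes/no has no dose. The tick boxes show the direction of a change without its size. A daily SOFA entry is at most one reading a day and not an amount given. None of them yields a cumulative total.

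**Size: inputs.** The documents give no norepinephrine durations. The nearest figure is the power model in Sample size and power: time T with vasopressors or hyperlactatemia among 30-day survivors is log-normal with mean 70 h in control, 70 − 18 = 52 h under the targeted effect, and SD 30 h. Mortality is 25 %. T includes hyperlactatemia, so it is an upper bound for time on norepinephrine.

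**Reproducing the plan's figure.** I simulated this model with 10,000 runs, deaths set to zero, a two-sided Mann-Whitney test and equal allocation (the last two are my assumptions). N = 194 gives power of 78.9 % against the planned 80 %, so the model is read as intended.

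**Still running at 72 h.** σ² = ln(1 + (SD/mean)²), μ = ln(mean) − σ²/2, and P(T > 72) = 1 − Φ((ln 72 − μ)/σ), with ln 72 = 4.277.

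- Control: σ = 0.411, μ = 4.164, z = 0.274, P = 0.392.
- Tissue perfusion: σ = 0.536, μ = 3.808, z = 0.875, P = 0.191.

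With SD 35 (the value in the source data) these are 38 % and 20 %. Averaged over arms, (39 + 19)/2 = 29 % of survivors, and 0.75 × 29 % = 22 % of all randomized patients, would have an incomplete total. If only half of them were on norepinephrine (an assumption), it would be 11 %. Both exceed the 5 % trigger for multiple imputation. Imputation has little to work with here, because no dose after 72 h is registered for anyone still infused.

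**Effect on the difference in raw means.** At a constant dose the total is proportional to min(T, c), where c is the cut. With a dose falling linearly to zero at T, it is T/2 if T ≤ c and c − c²/(2T) otherwise. Means are in units of starting dose × hours, SD 30:

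| Dose pattern | Cut (h) | Control | Tissue perfusion | Difference |
|---|---|---|---|---|
| Constant | 120 | 68.4 | 51.0 | 17.4 |
| Constant | 96 | 65.8 | 49.7 | 16.1 |
| Constant | 72 | 59.4 | 46.6 | 12.8 |
| Taper | 120 | 34.78 | 25.83 | 8.94 |
| Taper | 96 | 34.34 | 25.59 | 8.75 |
| Taper | 72 | 33.01 | 24.93 | 8.08 |

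Against the 120 h window the shrinkage is 1 − 12.8/17.4 = 26 % (constant) and 1 − 8.08/8.94 = 10 % (taper). Against 96 h it is 1 − 12.8/16.1 = 20 to 21 % and 1 − 8.08/8.75 = 8 %.

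**Effect on the test.** The Mann-Whitney probability that a control survivor's total exceeds a tissue-perfusion survivor's, ties counted as half, is 0.701 with the cut at 120 h and 0.701 at 72 h. If each patient also has an own dose level (assumed log-normal, CV 0.5 to 1, 75 survivors per arm), power falls by about 1 to 3 points under the taper and about 6 to 12 points at constant dose.

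**The case against.** The strongest reply is that absence from Appendix 4 does not prove that the doses will not be collected. The appendix is not a complete case report form: it has no item for hospital discharge, which the days-outside-hospital outcome needs. It says that data come from medical records and registers, the safety section says that charts hold detailed daily data, and the article refers to a full protocol that is not shown. This stands to the extent that the doses may well be retrievable, and a reader should not infer that the outcome is impossible to compute or that the data are lost. It does not remove the mismatch, because Appendix 4 does list the norepinephrine dose and gives it a window shorter than the outcome's.

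The size is also open to challenge, fairly. The proxy overstates norepinephrine time, the 26 % needs a constant infusion that stops abruptly, and the planned test is rank-based. The uneven loss between arms exists only if the hypothesis is true: with equal shock duration this model gives no differential loss. Where it does occur, it pulls towards no difference and does not favour the experimental arm.

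A reader might further infer that a patient who dies early will be scored as a low user, which would flatter an arm with more early deaths. No such rule is written. It would be an inference from silence on a matter often left to the full analysis plan. Equal mortality is assumed in both arms, and days alive without vasopressors is a separate outcome in which death already counts against the arm. The obvious remedies, ranking deaths worst or dividing by hours alive, would change what the outcome measures. I do not raise it.

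**Conclusion.** The outcome window and the listed dose-recording window disagree by 24 to 48 h, and no other listed item bridges them. That part rests on the text alone.

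The consequence rests on assumptions. Under the plan's survivor model, taken as an upper-bound proxy, about 39 % of control and 19 % of tissue-perfusion survivors would have totals cut short. If the hypothesis is true, the reported raw-mean difference would shrink by roughly 10 to 26 % on the 120 h reading, or 8 to 21 % on the 96 h reading. The Mann-Whitney result would change much less: not at all when patients differ only in duration, and by a modest loss of power when dose levels also vary.

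One secondary outcome is affected. It is worth correcting because it is the only dose-based measure of the first part of the hypothesis and the correction is cheap.

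**What to change.** In Appendix 4, extend registration of the norepinephrine dose to the end of day 5 after randomization in both arms, as an hourly rate or a daily total while the patient is on the drug, taken from charts or the patient data system. State in the outcome definition whether day 5 ends at 120 h from randomization or at the end of a calendar day. If collection cannot be extended, restate outcome i as the total up to 72 h, so that outcome and data agree.

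The cost is a little extra data entry, up to two further days and only for patients still receiving the drug. No treatment rule, primary analysis or sample size changes.

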### Primary outcome measure

Days alive in 30 days – with normal arterial blood lactate (first confirmed value of <2 mmol/L *and* without any inotropic or vasopressor agent)

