### Statistical plan and data analysis

#### Sample size and power

We assume 25 % mortality in both study groups, and this phase II trial will be unlikely to have the power to detect any mortality difference between the intervention groups. Therefore, a surrogate endpoint (days alive in 30 days with normal lactate and without vasopressors) combining survival, need for vasopressor therapy, and normalization of hyperlactatemia has been chosen. A post-hoc analysis from the FINNAKI study in a similar study population revealed a 30-day mortality rate of 25 %, and in 98 patients (of 128) who survived the mean time alive without vasopressors or hyperlactatemia within 30 days (720 h) was 650 h (SD 35) (unpublished data).

In the power analysis we assumed that the time with vasopressors or hyperlactatemia among the 30-day survivors follow a log-normal distribution with mean of 70 h (70 minus “treatment effect among survivors for the TTP group”) and SD 30, this simulated value was subtracted from 720 h (the number of hours in 30 days). For each configuration of sample size, mortality rate and expected treatment effect we simulated data and compared the two groups using a Mann-Whitney test. Ten thousand simulations were done for each configuration to compute the power. The required sample sizes (both groups combined) to achieve 80 % power as a function of mortality proportion (i.e., fraction of patients with a zero value for the primary endpoint) and average change in the primary endpoint among survivors are displayed in Table 1.

**Table 1 Tab1:** Power calculations

	Change among survivors in hours (and among all patients)		
Mortality proportion	12 h (9 h)	18 h (13.5 h)	24 h (18 h)
20 %	340	156	90
25 %	438	194	118
30 %	562	270	158
35 %	660	348	210
40 %	660	456	282

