The clinically relevant difference in the study primary outcome to be tested is 18 h (Amendment 1 to the study protocol – 26 October 2015). An adaptive sample size adjustment will be employed. After 150 patients have been included and followed for 30 days, the study statistician (Assoc. Professor [name], University of Copenhagen) will redo the power calculation based on the observed mortality proportion and the observed dispersion in the primary outcome. The calculation will be done without un-blinding the study and will follow the previous recommendation by Chow and Chang (based on the revised power calculation a suggestion for a revised sample size will be presented to the investigators) (https://www.crcpress.com/Adaptive-Design-Methods-in-Clinical-Trials-Second-Edition/Chow-Chang/9781439839874).

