### Statistical methods

The study flowchart is included as Fig. 1. A Mann-Whitney test for differences in continuous outcomes including the primary outcome measure, and Fisher’s exact test for dichotomous variables will be done as a primary analysis. A sensitivity analysis in subgroups of patients with and without previous hypertension will be performed. The components of the primary outcome measure (time to normalization of lactate, time to stopping of all vasoactive drugs, and day-30 mortality) are all included among secondary outcomes. In all tests a *p* value of less than 0.05 will be considered statistically significant. If missing data are >5 %, multiple imputations will be performed. A detailed statistical analysis plan is provided in Appendix 5.

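### After 72 h the text continues scheduled 2-hourly lactate in the TTP arm only, so a primary outcome that turns on the first normal lactate is biased slightly towards TTP

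*Protocol article*

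**What the plan says.** The section Primary outcome measure defines the outcome as "Days alive in 30 days – with normal arterial blood lactate (first confirmed value of <2 mmol/L", combined with freedom from any inotrope or vasopressor.

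Two places govern lactate measurement:

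- **Appendix 4 (Data to be registered)** lists arterial lactate, measured in both groups, at "Two-hour intervals (for 72 h unless study endpoint reached".
- **Appendix 2, Table 2** lists "Arterial lactate [7]/per 2 h" among the TTP primary targets. Its caption has targets registered hourly to 24 h and "every 2 h thereafter until study endpoint using tick boxes for targets". The MCG block of the table has no lactate row.

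On units, Sample size and power works in hours out of 720 and adds "The clinically relevant difference in the study primary outcome to be tested is 18 h". The outcome is named in days, with no rule for part-days. The 30-day list in Appendix 4 includes "Use of vasopressors? Y/N" as a daily item, and a matching one for inotropes.

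**The concern.** An endpoint reached at the first value below a threshold is dated by the sample that finds it. If one arm is sampled every 2 h and the other less often, the second arm's crossing is recorded later even when the true times are the same. Here the more closely sampled arm is the experimental one, and the difference falls on the patients with the longest shock.

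The trial is open-label. A blinded outcome assessor and a blinded statistician protect the reading of the data, but they cannot restore samples that were never drawn. A positive result could be challenged as partly a measurement artefact.

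A smaller matter is the unit. The effect sought among survivors, 18 h, is less than one day, so the time scale on which the outcome is computed should be explicit.

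**Working it through.** **Inputs from Sample size and power and Statistical methods.** Time with vasopressors or hyperlactatemia among survivors is log-normal with mean 70 h in MCG, 70 − 18 = 52 h in TTP, and SD 30 h. The outcome is 720 h minus that time, and 25 % of each arm score zero. The test is Mann-Whitney at the 0.05 level. Two-sided testing and 1:1 allocation are assumed, as neither is stated.

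**Step 1: reproduce the plan's figure.** Table 1 gives 194 patients for 80 % power at 25 % mortality and 18 h. Simulating the model as written (10,000 runs) gives power of about 0.79 at 194 and 0.80 at 200. The plan's figure is confirmed on the hour scale.

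**Step 2: how many survivors are unresolved at 72 h.** For a log-normal with mean m and SD s, σ² = ln(1 + (s/m)²) and μ = ln m − σ²/2.

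- MCG: σ² = ln(1 + (30/70)²) = 0.169, σ = 0.411, μ = 4.164. P(T > 72) = 1 − Φ((4.277 − 4.164)/0.411) = 39 %.
- TTP: σ² = ln(1 + (30/52)²) = 0.287, σ = 0.536, μ = 3.808. P(T > 72) = 1 − Φ((4.277 − 3.808)/0.536) = 19 %.

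**Step 3: size of the bias with no true effect.** Both arms have mean 70 h. After 72 h TTP is read every 2 h and MCG every g hours, where g is an assumption because the documents give no MCG interval. As a rough guide, the mean extra delay is (g − 2)/2 times the share unresolved: for g = 12, 5 × 0.39 ≈ 2.0 h; for g = 24, 11 × 0.39 ≈ 4.3 h. Simulation gives slightly more at long intervals, because crossing times bunch early in each interval. With 200 patients, if lactate is always the last component to resolve:

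| Assumed MCG interval | Shift, survivors | Shift, all patients (× 0.75) | Share of 18 h | Two-sided type I error |
|---|---|---|---|---|
| 6 h | 0.8 h | 0.6 h | 4 % | 0.050 |
| 12 h | 2.1 h | 1.6 h | 12 % | 0.051 |
| 24 h | 4.9 h | 3.7 h | 27 % | 0.068 |

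If lactate is last in only half of patients, the survivor shift is about 1.1 h at 12 h and 2.5 h at 24 h. Over the 12 to 24 h range and both assumptions, the one-sided error in favour of TTP is about 3 to 6 %, against a nominal 2.5 %. The two-sided figure hides much of this, because the error in favour of MCG falls at the same time.

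**Step 4: the unit.** Under the plan's model with a true 18 h effect and 200 patients, power is:

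- about 80 % when scored in hours;
- about 73 % when rounded up to 24-h blocks from randomization;
- about 71 % when scored in calendar days;
- about 80 % with hour data to 72 h and daily data afterwards.

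**The case against.** **TTP-only lactate is an inference.** It comes from joining a table caption about tick-box registration with a target row. Appendix 4 gives one 72 h limit for both groups, and Intervention accountability speaks of hourly target checks for 72 h. No text forbids lactate in MCG after 72 h, and routine care may well supply it. This stands as a limit on the size of the bias. It does not remove the problem. Read as written, Table 2 keeps the TTP target running to the endpoint. If TTP lactate also ended at 72 h, neither arm would have a schedule for an outcome that can be reached up to day 30. Both readings need the same repair.

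**The bias is small unless the assumptions are pressed.** This also stands. Lactate deciding every late case is an upper bound, and the documents do not say which component usually resolves last.

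**A reader might infer that the sampling asymmetry costs power.** It does not. It pushes the comparison towards TTP and raises apparent power, from about 0.80 to 0.82–0.86 at MCG intervals of 12 to 24 h.

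**A reader might also infer from the daily yes/no items that the outcome will be scored in whole days and the 80 % claim fails.** The documents do not support that. Every quantitative statement of the outcome is in hours. Norepinephrine and dobutamine doses are kept as 10-min medians for 72 h, and Trial interventions, Table 3 and Intervention accountability have treatment changes logged as they occur until the combined endpoint, up to day 30. The remaining gaps are narrow: other agents are not in the 10-min list, Table 3 has no explicit stop item, and the log ends at the endpoint, so a later restart shows only in the daily item.

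**Conclusion.** The point holds as a measurement bias in the primary outcome. Following Table 2 and Appendix 4 as written leaves scheduled lactate after 72 h in TTP alone, and the direction of the resulting bias favours TTP. The plan's own model puts about 39 % of MCG and 19 % of TTP survivors in the affected period.

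The size is modest and conditional. It is about 1 to 5 h among survivors for an assumed MCG interval of 12 to 24 h, depending on how often lactate is the last component to resolve, and under 1 h at 6 h. The calculation also assumes that lactate, once below 2 mmol/L, stays there.

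The unit is a clarification, not a failure of the power calculation. The drop to about 71–73 % would occur only under whole-day scoring, which the text does not prescribe.

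**What to change.** 1. Reconcile Table 2 and Appendix 4 so that lactate for outcome assessment follows one stated schedule in both arms until the combined endpoint is reached. This concerns measurement only and need not alter either arm's treatment targets. Cost: a few extra lactates in MCG patients still in shock after 72 h.
2. Alternatively, for deriving the endpoint only, evaluate lactate after 72 h in both arms on one common pre-specified grid, for example one fixed reading per day. Cost: coarser timing after 72 h, and a value must be available in MCG at each grid point. The last result in Step 4 suggests no material loss of power from daily resolution after 72 h.
3. State in Primary outcome measure and Appendix 5 that the outcome is computed in hours, as in the power calculation, from time-stamped lactates and from stop and restart times of every vasopressor and inotrope. Cost: a few added eCRF fields. Fix this before the blinded sample size recalculation after 150 patients, which uses the observed dispersion of the same outcome.
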